### Reporting of adverse events

All adverse events will be recorded and closely monitored until resolution or stabilization. In the event of any serious adverse event (≥ grade 3) [23], the event will be immediately reported to the Endpoint Adjudication Committee, which will determine the severity and causality of the adverse events. The chief investigator will be responsible for all adverse event reporting.

### Withdrawal from the trial

We will consider patient withdrawal from the trial if the following conditions occur: (1) severe brain swelling during the operation; (2) the patient has a cough during surgery; (3) the patient has persistent hypotension and circulatory instability.

### Data collection and management

All the patient information will be obtained through the electronic medical record system. The consent of the treating neurosurgeon, who will help us make the neurological diagnosis, will also be obtained. All personal information will be collected through the hospitalized medical records by a member of the research team and be kept strictly confidential for research purposes only. The research team members will be responsible for maintaining personal data. Only the primary investigator and the designated researcher can obtain interim results and final test data.

#### Data Monitoring Committee

The project will be monitored by a Data Monitoring Committee (DMC) composed of specialists in anesthesiology, ethics, statistics, and methodology. The DMC will audit through regular interviews or telephone calls.

### Sample size and justification

We calculated the sample size through the website http://www.sample-size.net/sample-size-proportions/.

The difference in brain oxygen saturation before and after surgery was 3.6 ± 4.1, α = 0.05, β = 0.2 [7]. Based on this, it can be calculated that the sample size required for our study is 44 cases. Considering a 20% shedding rate, a total of 53 participants (44 + 44*20%) need to be recruited. Due to the 1:1 distribution ratio, a total of 54 cases will be recruited.

### Statistics

The SPSS 19.0 software package for Windows (SPSS, Inc., Chicago, IL, USA) will be used for all statistical analyses. The quantitative variables will be expressed as mean ± standard deviation (SD) or median (interquartile range [IQR]) and analyzed by using the analysis of variance (ANOVA) or Mann-Whitney *U* test. Multiple comparisons among continuous variables at different time points will be performed using the Student-Newman-Keuls method for post hoc test. The incidence of reoperation rate will be expressed as the number of patients (percentage) and be analyzed by using the chi-square (χ^2^) test. *P* values < 0.05 will be considered to be statistically significant. After the follow-up of half of the cases, the interim analysis will be conducted to evaluate the validity of the main results.

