**Methods:**

This is a randomized controlled trial which will be carried out at the Second Affiliated Hospital of Soochow University. Fifty-four patients undergoing intracranial tumor surgery will be randomly allocated to the control group (C group) or the protective lung ventilation group (P group). In the C group, the tidal volume (VT) will be set at 8 ml/kg of predicted body weight, but positive end-expiratory pressure (PEEP) and recruitment maneuvers will not be used. In the P group, VT will be set at 6 ml/kg of predicted body weight combined with individualized PEEP during dura opening, while in other periods of general anesthesia, VT will be set at 8 ml/kg of predicted body weight. The level of rSO_2_, partial pressures of oxygen and carbon dioxide, oxygenation index, lactic acid level in arterial blood, and mean arterial pressure will be compared before anesthesia (T0), before dura opening (T1), after dura closing (T2), and 24 h after surgery (T3). Lung ultrasound scores will be measured at T0 and T3. The degree of brain relaxation at T1 and T2 will be evaluated by the surgeon using the brain relaxation scale. The amount of vasoactive drugs used and blood loss will be recorded during surgery. The duration of operation and reoperation rate will be recorded. The primary outcome of this study is the changes in rSO_2_ within 24 h postoperatively.

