**Fig. 1 Fig1:**
[figure not shown]
Schedule of enrollment, interventions, and assessments

**Table 1 Tab1:** Patient characteristics and baseline data

Characteristic	C group	P group
Male/female		
Age, years		
Body mass index (BMI), kg/m^2^		
Predicted body weight, kg		
American Society of Anesthesiologists (ASA) physical status, I/II		

Patients will be randomized after signed informed consent and confirmation of inclusion and exclusion criteria. Randomization will be conducted via a computer-generated age stratification randomized controlled table. Age stratification is according to (1) 18 < younger ≤ 40 years; (2) 40 < elder ≤ 65 years. Patients who meet the enrollment criteria will be randomly allocated to the control group (C group) or the PLV group (P group) within 24 h before surgery. The allocation ratio is 1:1. Permuted randomization will be used and stratified by age. The designated staff will perform the allocation sequence. The designated staff assistants will assign participants to the interventions. This research staff will implement the allocation sequence through sealed, opaque, and stapled envelopes. Corresponding envelopes will not be opened until the enrolled participants complete the trial. The anesthesiologist who is responsible for the anesthesia implementation will know the grouping but will not participate in the follow-up visit. However, the neurosurgeon who evaluates brain relaxation will be blinded to the group allocation. The patients and the outcome assessor are all blinded to the grouping.

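### Student-Newman-Keuls across T0 to T3 compares time points rather than arms, and no single between-arm test of the primary rSO2 outcome is fixed

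*Protocol article*

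**What the plan says.** The Statistics section of the protocol article assigns ANOVA or the Mann-Whitney U test to all quantitative variables. It does not say whether the ANOVA is one-way, two-way or repeated-measures. For the time points it states: "Multiple comparisons among continuous variables at different time points will be performed using the Student-Newman-Keuls method for post hoc test". Each test is judged at P < 0.05, and none is labelled as primary.

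On the outcome, the article says: "The primary outcome of this study is the changes in rSO_2_ within 24 h postoperatively". It refers to Table 2, which sets out rSO2 by arm at T0, T1, T2 and T3. The abstract's objective uses a different window, Ta to Tb, whose limits are not among these four times.

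On the design: "The allocation ratio is 1:1" and "Permuted randomization will be used and stratified by age". The sample size section starts from a before-after difference of 3.6 ± 4.1 and concludes that "the sample size required for our study is 44 cases".

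**The concern.** The only procedure named specifically for the time points does not answer the randomised question. SNK across T0 to T3 asks whether rSO2 differs between times. The trial asks whether it differs between arms. SNK is also designed for independent means, whereas these are four readings per patient, and it does not hold the family-wise error when there are several means.

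A between-arm test is available in the text (ANOVA with two groups, or Mann-Whitney U), but it is tied to no time point and no change score. The reader cannot tell which P value decides the trial. Two of the four possible arm comparisons, T0 and T1, come before the ventilation of the arms differs.

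The section also mentions neither covariate adjustment for baseline rSO2 nor the age stratum used in randomisation. In a trial of 54 patients that gives up precision that costs nothing to obtain.

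**Working it through.** **1. The plan's own figure.** Inputs from the sample size section: difference 3.6, SD 4.1, α 0.05, β 0.2. I take α as two-sided, since sidedness is not stated.

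- Normal approximation: n per arm = 2 × (1.960 + 0.842)² × 4.1² / 3.6² = 20.4, so 21.
- With the t distribution: 21.4, so 22 per arm and 44 in total. This is the stated figure.
- Alternatives do not fit: one-sided needs 17 per arm, and a paired before-after test needs about 13 in all.

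The 44 therefore presumes one two-sample comparison of one change. The Statistics section never specifies that test.

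**2. SNK even with independent data.** Take four means that form two well-separated pairs, each pair truly equal. SNK tests each pair at 5%, so the chance of at least one false rejection is 1 − 0.95² = 9.75% (simulated: 9.8%). This shows a property of the procedure. It does not predict the error rate in this trial.

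**3. What follows if the four readings are pooled as independent.** The documents give no within-patient correlation, so r is assumed. Setting: 22 per arm, four times, equal correlation between all times, no true effect.

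The variance of the arm difference averaged over four readings is (1 + 3r) times what an independent-data analysis supposes. The false-positive rate is about 2Φ(−1.96/√(1 + 3r)).

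| r | closed form | simulated |
|---|---|---|
| 0.3 | 15.5% | about 15% |
| 0.5 | 21.5% | about 21% |
| 0.7 | 26.6% | about 27% |

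The same error acts the other way on comparisons of times. In simulation the arm-by-time interaction is significant in only 1.3% / 0.2% / under 0.1% of trials, and the time effect within one arm in 1.4% / 0.3% / about 0%. Those tests lose power.

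**4. What follows if the arms are tested separately at T2 and T3, unadjusted.** The chance of at least one P < 0.05 is about 10% / 9% / 8.5% at r = 0.3 / 0.5 / 0.7. Repeated simulations varied by a few tenths of a percentage point.

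**5. What adjustment for baseline gains.** With equal variance σ² at both times, a change score has variance 2σ²(1 − r) and ANCOVA has σ²(1 − r²). The ratio is (1 + r)/2. Taking 4.1 as the SD of the change, with 22 per arm and the t distribution:

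| analysis | variance factor | power |
|---|---|---|
| change score | 1 | 0.81 |
| ANCOVA, r = 0.3 | 0.65 | 0.94 |
| ANCOVA, r = 0.5 | 0.75 | 0.91 |
| ANCOVA, r = 0.7 | 0.85 | 0.87 |

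**The case against.** A reader might infer that the primary analysis is an ANOVA that ignores within-patient correlation, makes no use of baseline and so runs a false-positive rate of 15% to 27%. The documents do not support that, for four reasons.

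- **Type of ANOVA.** It is not stated. A repeated-measures ANOVA is not excluded, SNK can be computed with a repeated-measures error term, and a condensed article commonly leaves the model to a fuller document. The text makes no provision for repeated measures, but silence does not show that the correlation is ignored.
- **Between-arm test.** Mann-Whitney U is a between-arm test and is named. What is missing is its assignment to one time or change.
- **Baseline.** The primary outcome is a change, and the sample size rests on a before-after difference, so baseline may enter by subtraction. A change-score comparison is valid in a randomised trial. The case for ANCOVA is one of precision.
- **Age stratum.** Covariate lists are often left to an analysis plan. Omitting a two-level stratum mainly costs precision, and no figure in the document links age to rSO2. This is a minor point.

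All four stand as limits. They do not remove the two defects in what the text does state: SNK is named for comparing repeated readings over time, and no one between-arm contrast decides the primary outcome. An analysis plan that repaired the first would have to contradict the article.

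**Conclusion.** The point holds in this limited form and should be acted on. SNK is the wrong tool for T0 to T3 and answers a question about time, and the single comparison that the 44 cases were sized for is not written into the Statistics section.

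The error rates are conditional. About 15% / 21% / 27% applies only if the readings are pooled as independent, which the article does not say. About 8% to 10% applies only if unadjusted arm tests at T2 and T3 both count as primary. Both rest on an assumed correlation of 0.3 to 0.7 with equal correlation between times. The gain in power from 0.81 to between 0.87 and 0.94 rests on the same assumed range, on equal variances, and on reading 4.1 as the SD of the change.

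**What to change.** In the Statistics section:

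1. Delete Student-Newman-Keuls.
2. State one primary between-arm test: an ANCOVA of rSO2 at one named post-intervention time on arm, baseline rSO2 (T0) and age stratum, reported as the adjusted difference with its 95% CI. If the outcome within 24 h after surgery is kept, that time is T3. An ANCOVA of the change from T0 gives the same arm estimate, so the wording of the outcome as a change can stay.
3. Analyse the other times of rSO2, and MAP and blood gases, as secondary with a linear mixed model (arm by time, baseline, age stratum).

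The Ta to Tb window in the abstract's objective must be reconciled with the primary outcome before the time is fixed. That is a decision about the outcome, and the analysis wording cannot settle it.

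Otherwise the cost is analysis wording only. rSO2 at T0 and T3 and age are already collected, and the sample size does not rise.

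### The interim analysis of the main results has no stated purpose and no threshold other than P < 0.05, and its results are reserved to investigators: about 8.3% type I error if significance at either look counts

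*Protocol article*

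**What the plan says.** Four places in the protocol article bear on this point.

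- **Statistics, timing and subject.** "After the follow-up of half of the cases, the interim analysis will be conducted to evaluate the validity of the main results". The subject is the main results. No purpose, stopping rule or boundary is given.
- **Statistics, threshold.** The sentence just before sets the only significance criterion in the article: P "values < 0.05 will be considered to be statistically significant". It makes no distinction between interim and final analysis.
- **Sample size and justification.** "The difference in brain oxygen saturation before and after surgery was 3.6 ± 4.1, α = 0.05, β = 0.2", from which "the sample size required for our study is 44 cases". This rises to 53 for dropout and to 54 for 1:1 allocation. One α of 0.05 is used.
- **Access.** Under Data collection and management: "Only the primary investigator and the designated researcher can obtain interim results and final test data". Under Data Monitoring Committee, a committee that includes statistical and methodological expertise monitors the project, and its activity is described as follows: "The DMC will audit through regular interviews or telephone calls". No role in the interim analysis is mentioned.

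**The concern.** A look at the primary comparison half-way gives a second chance of a false-positive result unless the two looks share the 5%. Here the stated criterion is 0.05 throughout, and the sample size already spends the whole 5% on one test. Someone who follows the article as written could declare significance at either look and still report a 5% test.

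The access sentence raises a second problem, about trial conduct. The trial is single-centre and recruits continuously, so patients are still being enrolled when the interim is read. Some exits after randomization depend on judgement: the termination and withdrawal criteria include brain swelling and circulatory instability, and the Discussion says that abandoned cases are reported to the principal investigator. If the people running the trial know how the rSO2 comparison stands, that knowledge can influence recruitment, exclusions and the decision to continue. The body normally placed to hold such results exists in this trial, but the wording does not let it have them.

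**Working it through.** **1. Does the planned sample size use the full 5% on one test?**

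Inputs from Sample size and justification: difference 3.6, SD 4.1, α = 0.05, β = 0.2. Sidedness is not stated, so two-sided is tried first.

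- Normal approximation: n per arm = 2 × (1.960 + 0.842)² × 4.1² / 3.6² = 2 × 7.85 × 16.81 / 12.96 = 20.4, so 21 per arm and 42 in total.
- Two-sample t-test: power is 79.3% with 21 per arm and 81.2% with 22 per arm. So 22 per arm, 44 in total, which is the article's figure.
- Variants that do not fit: one-sided 34 in total, 90% power 56 in total, paired design about 11.

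The stated 44 is therefore a two-sided, two-sample comparison with a single test at 0.05. Nothing is reserved for an interim look.

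**2. Overall type I error if significance at either look counts**

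Let Z1 and Z2 be the test statistics at the interim and final looks, and t the information fraction at the interim. Under the null hypothesis they are bivariate normal with correlation √t, and

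overall error = 1 − P(|Z1| < c1 and |Z2| < c2).

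With c1 = c2 = 1.960 (two-sided 0.05 at both looks):

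| Information fraction t | Overall type I error |
|---|---|
| 0.4 | 8.63% |
| 0.5 | 8.31% |
| 0.6 | 7.96% |

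At t = 0.5 the interim look contributes 5.00%, and the final look adds 8.31 − 5.00 = 3.31 percentage points. Half of the cases may mean 27 of the 54 recruited or 22 of the 44 evaluable. Both are t = 0.5, and the table shows that modest departures change little.

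Because the samples are small, this was checked by simulating t-tests (400,000 trials per scenario): 8.37% for 11 then 22 per arm, 8.47% for 13 then 27, and 8.30% for 14 then 27.

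**3. Boundaries that hold about 5% at t = 0.5**

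| Boundary | Interim P | Final P | Overall |
|---|---|---|---|
| O'Brien-Fleming (|Z| > 2.797, then 1.977) | 0.0052 | 0.0480 | 5.00% |
| Pocock (|Z| > 2.178 at both) | 0.0294 | 0.0294 | 5.00% |
| Haybittle-Peto | 0.001 | 0.05 | 5.02% |

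With 22 per arm, difference 3.6 and SD 4.1, normal-approximation power is 82.9% for one test at 0.05 and 82.7% with the O'Brien-Fleming limits.

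**4. Access, set side by side**

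The data management section opens interim results to two roles and uses the word only. The DMC section creates an independent committee with statistical expertise and describes audit by interview or telephone. Taken literally, the first excludes the second from the interim results, and nothing elsewhere in the article restores access.

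**The case against.** The strongest reply is that the article never says the interim look is a hypothesis test. The 0.05 criterion is a general convention for all analyses. The interim sentence names no test, no threshold and no right to stop or claim success, and the validity of the main results could refer to data quality or assumptions as well as to efficacy. The termination and withdrawal criteria concern individual patients, not the trial. A look used only for futility or conduct, or never acted on for efficacy, keeps the error at or below 5%. This stands: a reader might infer that the protocol prescribes two tests at 0.05 and so has an 8% error rate, but the text does not go that far.

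Boundaries are also often left to an analysis plan or a DMC charter, and neither is shown. This stands in part, because a missing boundary alone would be no finding. But the article does fix something: one unqualified threshold next to the interim sentence, a sample size with the whole 5% on one test, and an access rule. A boundary set elsewhere would have to be reconciled with the first, and DMC review of interim results would contradict the last.

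On access, a reader might infer that the plan deliberately bypasses the DMC and unblinds the investigators. The documents do not support this. The access sentence closes a paragraph on confidentiality and may be meant to limit access within the research team. The DMC is said to monitor the project, and the audit sentence does not say that it receives no data. Nothing says that the interim report is by arm. The randomization text keeps envelopes closed until enrolled participants complete the trial, and it blinds patients, the outcome assessor and the neurosurgeon who rates brain relaxation. What remains is the literal wording, which excludes the DMC and does not keep comparative results from the investigators.

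**Conclusion.** The concern holds in a conditional form. As worded, the plan allows two looks at the main result at 0.05 each. If a significant result at either counts as positive, the overall two-sided type I error is about 8.3% (8.0% to 8.6% for information fractions of 0.6 to 0.4). This figure assumes one between-group test of the primary outcome at each look and no adjustment. Without an efficacy claim at the interim, the 5% is kept.

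The access point does not depend on that condition: the text reserves interim results to two investigator roles while recruitment continues and, read literally, shuts out the DMC. Whether those results would be comparative is not stated, so the risk to trial conduct is real but cannot be quantified. Both points should be settled before the interim is run, since a look cannot be undone.

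**What to change.** - **Purpose.** State in the Statistics section what the interim analysis is for and what decisions may follow from it.
- **Error rate.** Choose one of two routes. (a) State that the interim makes no efficacy claim and covers safety and conduct only, with the final test at 0.05. (b) Keep an efficacy test and state a boundary that holds 5% overall, for example O'Brien-Fleming with P < 0.005 at the interim and P < 0.048 at the end. Pocock and Haybittle-Peto limits are alternatives.
- **Access.** Amend the data management sentence so that any comparative interim results go to the existing DMC and not to the investigators before the final analysis, and add the interim review to the DMC's described role.

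The cost is small. Route (a) leaves the final threshold unchanged. Route (b) with O'Brien-Fleming limits moves it from 0.050 to 0.048, costs about 0.2 percentage points of power (82.9% to 82.7%) and adds no patients. DMC-only reporting takes some work: someone who does not run the trial should prepare the report, and the committee's task must be defined while the trial is already recruiting.

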## Discussion

This study is a single-center, randomized controlled trial exploring whether protective lung ventilation (PLV) during intraoperative dura opening can improve regional cerebral oxygen saturation (rSO_2_) in neurosurgical patients.

The incidence of postoperative pulmonary complications (PPCs) is high due to the long mechanical ventilation in neurosurgery. Qaseem et al. [24] reported that the risk of PPCs increased when the operation time is more than 4 h. The incidence of PPCs was 28.4% (20.2–37.9%) in patients with neurosurgery lasting for longer than 300 min [25]. PEEP can lower the incidence of postoperative respiratory complications, prevent atelectasis, and reduce the risk of ventilators associated with lung injury.

In this study, individual PEEP (< 10cmH_2_O) will be used to avoid the effect of high PEEP on intracranial pressure (ICP). It is a crucial issue that PEEP can be safely used in craniotomy. Therefore, pulmonary protective ventilation will be performed during dura opening, and cerebral relaxation will be assessed before dura incision. If the ICP is elevated enough to affect the operation for using PEEP, we will abandon the case and change the ventilation parameters. The case will be reported to the principal investigator.

The rSO_2_ is actually the mixed oxygen saturation of local brain tissues, which can better reflect the change of brain oxygen supply and consumption balance during the perioperative period. Samra et al. [26] studied 100 patients who underwent carotid endarterectomy. They found that if the rSO_2_ value decreased by 20% compared with the baseline value after internal carotid artery occlusion, it predicted the possibility of neurological complications, and indicated that its sensitivity was 80% and its specificity was 82%. Since the ratio of cerebral blood volume to arterial/venous blood flow is approximately 20:80, the NIRS value mainly represents cerebral venous oxygen saturation, which is completely unaffected by hypoxemia and hypocarbonemia, and better reflects the changes in the balance of oxygen supply and consumption in the brain [27]. Near infrared spectroscopy (NIRS) as a brain oxygen monitoring method has the following characteristics: it is continuous and noninvasive and convenient, and it has a high degree of sensitivity and specificity [28]. Monitoring rSO_2_ can detect changes of the cerebral blood flow and oxygen supply and consumption balance in the brain area as early as possible, and judge the degree of cerebral ischemia and hypoxia and changes in brain function. Timely adjustment of the anesthesia plan is helpful to guide perioperative anesthesia management, so as to prevent POCD, shorten the hospitalization period, and improve quality of life.

We focus on whether a pulmonary protective ventilation strategy can affect cerebral venous reflux and brain tissue oxygenation and, ultimately, the prognosis of patients. PLV after incision of the dura can reduce the returned blood volume that results in exposing potential bleeding spots, which is beneficial in helping the surgeon to stop bleeding. Due to the opening of the dura, the ICP disappears, and the decreased cerebral perfusion pressure caused by the expansion of the lung is improved.

This study is a prospective, randomized controlled trial. This study aims to investigate the effect of intraoperative pulmonary protective ventilation in neurosurgical craniotomy. If we are able to demonstrate the safety and effectiveness of intraoperative pulmonary protective ventilation with individualized PEEP during dura opening in neurosurgical craniotomy, it will improve the prognosis of patients undergoing neurosurgery and reduce medical costs.

